### Randomization and blinding

The included patients will be randomized to one of the two groups (OFA or standard of care) using a web-based system (Ennov Clinical® software) by the investigator anesthesiologist in charge on the day or the day before the scheduled surgery.

Patients will be randomized in one of the two groups with a 1:1 ratio, using a minimization algorithm defined by the randomization methodologist (with a probabilistic component), based on two factors: the type of surgery (ENT, plastic, digestive, urologic and gynecologic surgery) and the surgery severity (assessed by the Surgical Outcome Risk Tool (SORT) score, which can be classified in minor, intermediate, major and major/complex surgery, and which is available online at www.sortsurgery.com). Investigators do not know this equation and will not be able to guess the next randomization arm.

The anesthesia team performing the general anesthesia will be unblinded on the allocation group. The patient will be kept blinded to the protocol allocation, as the nurses and the medical team involved in the postoperative care and outcomes evaluation. For outcomes requiring a phone call, evaluators will be blinded to the allocation group.

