#### Secondary outcomes

In order to confirm the impact of the OFA protocol on postoperative recovery, we will also measure the QoR-15 score at 48 h and 72 h after the surgery in all patients. We will evaluate the pain during effort (mobilization, cough or physiotherapy sessions) and the number of postoperative complications according to the POMS (postoperative morbidity survey) classification [27], assessed up to 72 h after the surgery. The postoperative consumption of morphine-equivalent will also be compared between the two groups. The lengths of stay in PACU and in the hospital will be measured.

We will compare the patient tolerance to the allocated protocol with the assessment of the hemodynamic status (intra-operative use of vasopressor or cessation of one of the drugs for hemodynamic purposes), heart-rhythm (< 35 or > 140 beats per minute for more than 30 s), and anaphylactic reactions. Another secondary outcome is the respect of the allocated protocol by the anesthesia team: OFA protocol will be considered complete if at least two of the following drugs are used between ketamine, lidocaine, clonidine, and magnesium sulfate, and if no intraoperative opioids are used; the standard group will be considered complete if lidocaine, clonidine, or magnesium sulfate are not used intra-operatively. The surgeon’s and anesthesiologist’s satisfactions concerning the anesthesia will be assessed after the surgery according to a numerical scale (rated from 0 to 10). We will also compare the patient satisfaction of anesthesia at 24 h via a numerated scale from 0 to 10 (0 = not satisfied and 10 = totally satisfied) and the presence or absence of intra-operative memorization.

Three months after surgery, a phone interview will be conducted to evaluate the chronic pain using the Brief Pain Inventory (BPI) [28] in its French short version, the quality of life using the French EQ-5D-3 L questionnaire (available on request on https://euroqol.org/), and the rate of neuropathic pain diagnosed using the DN-4 questionnaire [29].

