For each of the analyses involving the multiple imputation method, sensitivity analyses will be performed if the missing data rate for the endpoint of interest is greater than 10%. We will conduct an analysis only on the complete cases, as well as best-worst and worst-best case sensitivity analyses. For the best worst-case scenario, it is assumed that all participants lost to follow-up will have a beneficial outcome; and all those with missing outcomes in the other scenario will have a harmful outcome. For continuous outcomes, the beneficial outcome will be the group mean plus one standard deviation of the group mean, and the harmful outcome will be the group mean minus one standard deviation of the group mean [31]. To eliminate the potential risk of a violation of the normality, we will confirm the results for continuous variable implicating in the hierarchical scheme by sensitivity analysis using a semi-parametric approach with an ordinal model [32].

Concerning the pain evolution and morphine consumption variation, we will analyze those outcomes using a mixed effects linear regression model (fixed effect for the treatment arm, a fixed effect for the time frame, a fixed effect for each minimization factor, and a random effect for the patients). Hospital and PACU length of stays, as well as satisfactions (those of the surgeon, those of the anesthesiologist, those of the patient), will be compared using a linear regression model (allocation group and minimization factors as covariates). The proportion of complications of the POMS will be defined as a categorical variable (four levels: no complication, one complication, two complications, and more than 3 complications) and will be analyzed using a logistic regression model (allocation group and the minimization factors as covariates). The rate of patients presenting neuropathic pain, as well as the proportion of patients experiencing memorizations, will be compared by logistical regression models (allocation group and the minimization factors as covariates). Pain characteristics described by BPI and the proportion of patients in each of the five scales of EQ-5D will not be compared but only described.

All statistical analyses will be performed by two-sided tests. The signification cutoff will be a *p* value < 0,05 with 95% confidence interval.

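### The POMS outcome levels omit exactly three complications, and the form of logistic regression for this four-level variable is not named

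*Protocol article*

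**What the plan says.** Under Secondary outcomes, the protocol article lists "the number of postoperative complications according to the POMS (postoperative morbidity survey) classification", assessed up to 72 hours after surgery, so the endpoint starts as a count. Under Statistical analysis the count becomes a categorical variable with "four levels: no complication, one complication, two complications, and more than 3 complications". That variable "will be analyzed using a logistic regression model (allocation group and the minimization factors as covariates"). The article gives no reference level, no cut-point and no statement that the model is ordinal or multinomial.

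The same paragraph covers intra-operative recall, which Secondary outcomes defines as "the presence or absence of intra-operative memorization". Here "the proportion of patients experiencing memorizations, will be compared by logistical regression models (allocation group and the minimization factors as covariates"). The article gives neither an expected recall rate nor a rule for few or no events.

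The covariates come from Randomization and blinding. The first minimization factor is "the type of surgery (ENT, plastic, digestive, urologic and gynecologic surgery"). The second is the SORT severity class, "which can be classified in minor, intermediate, major and major/complex surgery".

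**The concern.** The levels run 0, 1, 2 and then above 3. Three is an ordinary value of a complication count, so the coding rule fails for some patients who are likely to be among the sicker ones. Multiple imputation is reserved for the endpoints in the hierarchical testing scheme, and POMS is not listed for it. The analyst must therefore either leave these patients out or decide later where they go.

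The model adds a second open choice. A proportional-odds model gives one treatment odds ratio, a multinomial model gives three, and a binary model needs a cut-point that the article does not state. These choices are best fixed before allocation is revealed.

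For recall, a model adjusted for arm, surgery type and severity needs events in both arms to give a finite arm odds ratio. Whether this is a problem depends on a rate that the article does not state.

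**Working it through.** **Planned size.** Inputs from Sample size: difference 8, SD 16, two-sided alpha 0.05, power 0.80, 10% unavailable.

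- Per arm: n = 2 × (1.960 + 0.842)² × 16² / 8² = 2 × 7.85 × 4 = 62.8, so 63 per arm and 126 in total.
- With 10% unavailable: 126 / 0.90 = 140.

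Both match the article. The article states no figure for POMS or recall, so the rates below are illustrative assumptions.

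**POMS levels.** The possible counts are 0, 1, 2, 3, 4 and up. The stated levels cover 0, 1, 2 and 4 upward, so only 3 is missing. To show the possible scale, assume a Poisson count with mean λ, so that P(exactly 3) = e^(−λ) λ³ / 6, and multiply by 140:

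| Assumed λ | P(exactly 3) | Expected with exactly 3 | Expected with more than 3 |
|---|---|---|---|
| 0.5 | 0.013 | 1.8 | 0.2 |
| 1 | 0.061 | 8.6 | 2.7 |
| 1.5 | 0.126 | 17.6 | 9.2 |
| 2 | 0.180 | 25.3 | 20.0 |

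At each of these means, more patients would be unclassified than would fill the stated top level.

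**POMS model form.** With five surgery types and four severity classes, the covariate terms number 1 (arm) + 4 (type) + 3 (severity) = 8.

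- Proportional odds: 3 thresholds + 8 = 11 parameters, one treatment odds ratio.
- Multinomial: 3 × (1 + 8) = 27 parameters, three treatment odds ratios.
- Binary: 1 + 8 = 9 parameters, with an unstated cut-point.

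If urologic and gynecologic surgery form one type, there are 7 covariate terms and the totals become 10, 24 and 8.

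**Recall.** Assume rate p in both arms, with 70 patients each. The chance that at least one arm has no event is 2(1 − p)^70 − (1 − p)^140.

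| Assumed p | Expected events in 140 | P(no event at all) | P(at least one arm has none) |
|---|---|---|---|
| 0.1% | 0.14 | 0.869 | 0.995 |
| 0.5% | 0.70 | 0.496 | 0.912 |
| 1% | 1.40 | 0.245 | 0.745 |
| 2% | 2.80 | 0.059 | 0.427 |
| 5% | 7.00 | 0.001 | 0.054 |

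At 2%, for example, 0.98^70 = 0.243 and 0.98^140 = 0.059, so 2 × 0.243 − 0.059 = 0.427. With 63 per arm, the last column becomes 0.996, 0.927, 0.780, 0.482 and 0.077.

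**The case against.** The strongest reply is that the level gap is a slip of wording. A variable running none, one, two and then a top class is naturally read as ending in three or more, and the analyst would probably code it so. That is likely what was meant. Even so, the article does state the levels, and states them wrongly, so this is not a detail left to a fuller plan.

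On the model, a reader might infer that the POMS analysis cannot be run at all because logistic regression takes only two levels. The document does not support this. Ordinal and multinomial models are also logistic regressions, and nothing in the text implies that the four levels will be collapsed. What remains is an unnamed form, which an analysis plan could settle. The text does not point to the ordinal form either. It mentions an ordinal model only as a sensitivity analysis for continuous endpoints in the hierarchy, and it uses the plain term logistic for the binary endpoints in the same paragraph.

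On recall, a reader might infer that the adjusted model is not estimable, or that one arm will usually have no events. Both rest on a rate that the document never gives. At an assumed 2% the chance of an empty arm is already below one half, and at 5% it is about 1 in 20. Separation confined to one surgery type or severity class need not destroy the arm estimate. The article also commits to reporting absolute as well as relative measures, so recall need not go unreported if a fit failed. Only the conditional form stands.

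**Conclusion.** The coding defect is plain from the text and needs no assumption: a count of exactly three has no level. How many patients this affects is unknown, and the Poisson figures only illustrate it. The unnamed model form is a smaller gap, worth closing in the same sentence. The recall point holds only if recall is rare, at about 2% or less. There the chance that at least one arm is empty runs from about 43% up to 99.5%, and the adjusted arm effect may have no finite estimate.

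The weight is minor. The article reserves imputation for hierarchy endpoints and names QoR-15, chronic pain by the BPI and the EQ-5D visual analog score for it. POMS and recall therefore appear to lie outside the hierarchy, although the hierarchy figure is not available to confirm this. The primary analysis, the sample size and the type I error scheme do not depend on either endpoint.

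**What to change.** - **POMS levels:** define them as 0, 1, 2 and 3 or more, so that every count has a level.
- **POMS model:** name a proportional-odds (ordinal) logistic model with allocation group and the two minimization factors as covariates, reporting one treatment odds ratio with its 95% confidence interval. The small downside is reliance on the proportional-odds assumption.
- **Recall:** state in advance that, if events are sparse, recall will be reported as counts per arm with an exact test and an exact interval. The analysis plan should say what counts as sparse. The price is that this comparison is then not adjusted for the minimization factors.

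All three are changes of wording, best made before allocation is revealed. They need no extra patients, visits or data.

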### Type I error management

We will manage the type I error in a sequential hierarchical manner (Fig. 4). We will test the first endpoint (i.e., QoR-15 at H24), and if the *p* value is less than 0.05, we will conclude that there is evidence of an effect. Then, we will test the following endpoint (i.e., QoR-15 at H48) using a significance level of 0.05. We will continue to test each endpoint of the hierarchical classification either up to the last endpoint (i.e., the quality of life by the EQ-5D visual analog scale at 3 months) or if we observe a non-significant result. Suppose a non-significant result (*p* value > 0.05) for one of the endpoints is observed. In that case, we will perform the following statistical comparisons in an exploratory manner without drawing any clinical conclusion.

**Fig. 4 Fig4:**
[figure not shown]
Diagram of the hierarchical classification of the statistical tests (type I error management). OFA, opioid-free anesthesia; VAS, visual analog scale

No interim analysis is planned during the inclusion period.

## Discussion

Although OFA seems promising in the context of the opioid crisis, data are needed to objective its interest; our study will be powered to evaluate the impact of OFA on early QoR and give useful information on long-term benefit of reducing perioperative opioid use. In addition, we choose to use a combination of lidocaine, magnesium sulfate, ketamine, and clonidine to perform OFA. Other studies are underway which attempt to evaluate the quality of postoperative recovery using OFA, but either do not fully assess this “full” combination of drugs [33], or do not propose a continuous infusion throughout surgery [34]. In addition, we plan to evaluate OFA in a wide range of surgeries, while other studies focus on one type of surgical procedure only, in order to provide more generalizable results.

We choose to combine these different pharmacological classes during surgery for their different effects: analgesia, anti-hyperalgesia, anti-inflammatory effect, anti-nausea and anti-vomiting, and reduction of the neurohumoral stress response. In the anesthesia literature, different OFA protocols were described [35]. While OFA using dexmedetomidine has been reported to be effective during several types of surgery [13, 36], it may promote side effects, including increased risk of bradycardia and hypoxemia [9]. We thus prefer to incorporate clonidine as an alpha-2 agonist agent in our OFA protocol, because this molecule seems to be less responsible for severe bradycardia episodes [37] and seems to have longer positive effects [38].

To evaluate OFA, we choose primary criteria focused on patients’ overall recovery. Indeed, in a recent international consensus, the SteP–COMPAC group has highlighted the value of postoperative recovery scales for standardizing outcomes in perioperative medicine [25]. The QoR-15 questionnaire appears reliable, sensitive, and easily achievable in clinical practice (2 to 3 min for the questionnaire to be fully completed). It gives information on postoperative recovery in a unidimensional approach, and the patient can complete the questionnaire alone or with the help of an assessor. Therefore, different studies have used this questionnaire to evaluate the impact of an intervention on patients’ perception of postoperative recovery [26]. Beyond assessing the quality of early recovery, we will also study the longer-term status (i.e., at 3 months). The study aims to investigate the pain profile of the patients, detect the presence of chronic pain, neuropathic pain, and estimate their quality of life. To our knowledge, our study would be the first to evaluate OFA on these long-term criteria.

In a nutshell, this study will compare an OFA protocol (based on a combination of four agents: clonidine, ketamine, magnesium sulfate, and lidocaine) versus a standard anesthesia protocol in patients scheduled for major non-orthopedic surgery, on their early QoR but also on their pain status and their quality of life at 3 months. The findings will also provide evidence of potential adverse events associated with this OFA protocol, helping to assess the benefit/risk ratio of the use of such a pharmacological combination.

## Trial status

This study was approved by the French Institutional Review Board “Eastern III” (Nancy, France, number: 2021-A00364-37) and the National Agency for Drug and Health Product Safety, and registered at ClinicalTrials.gov (NCT04797312) on 15 March 2021. The recruitment of participants started in July 2021. The anticipated period is 18 months.

## Data Availability

The data generated could be shared after a request to the corresponding author. Three years after the end of follow-up of the last included patient, we will deliver a completely deidentified dataset to an appropriate data archive for sharing purposes.

## Abbreviations

BPI: Brief Pain Inventory
ENT: Ear, nose, and throat
EQ-5D: Euroqol-5D score
IV: Intravenous
OFA: Opioid-free anesthesia
PACU: Post anesthesia care unit
PCA: Patient-controlled analgesia
POMS: Postoperative morbidity survey
PONV: Postoperative nausea and vomiting
QoR: Quality of recovery
SORT: Surgical Outcome Risk Tool
